### Suspected unexpected serious adverse reactions (SUSAR)

Adverse reactions are all untoward and unintended responses to an investigational product related to any dose administered.
Unexpected adverse reactions are adverse reactions, of which the nature, or severity, is not consistent with the applicable product information (e.g. Investigator’s Brochure for an unapproved IMP or Summary of Product Characteristics (SPC) for an authorized medicinal product).
The sponsor will report expedited the following SUSARs to the METC:

SUSARs that have arisen in the clinical trial that was assessed by the METC;

SUSARs that have arisen in other clinical trial of the same sponsor and with the same medicinal product, and that could have consequences for the safety of the subjects involved in the clinical trial that was assessed by the METC.

The remaining SUSARs are recorded in an overview list (line-listing) that will be submitted once every half year to the METC. This line-listing provides an overview of all SUSARs from the study medicine, accompanied by a brief report highlighting the main points of concern.

The sponsor will report expedited all SUSARs to the competent authority, the Medicine Evaluation Board and the competent authorities in other Member States and to Wörwag Pharma GmbH & Co. KG.

The expedited reporting will occur not later than 15 days after the sponsor has first knowledge of the adverse reactions. For fatal or life threatening cases the term will be maximal 7 days for a preliminary report with another 8 days for completion of the report.

For all events that may require the unblinding of participant treatment, the medical monitor must be contacted before the unblinding occurs. In all cases, the medical monitor will notify the protocol chairs and the medical officer.
Any treatment unblinding will require a full written account. The account will include the reason for unblinding the study medication, the name of the medical monitor notified of the unblinding, and the date and time of the unblinding. The reasons for unblinding each individual study treatment should be included on the Treatment Unblinding Case Report Form and in the final study report. If a participant is unblinded, study therapy is discontinued and the participant is terminated from the study.

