## Randomisation, blinding and treatment allocation

The treatment phases of 3 months is performed in a double-blind design. Active medication and placebo have identical appearance and can be identified within this study only by the randomizing list.

A randomizing list will be prepared by [name]. [name] (independent statistician, University of Ulm, Germany) and sent to the manufacturer of the study medication for packaging. The randomizing list is to be stored strictly closed and must not be seen by anyone else than the packaging employee. After packaging, it has to be sealed and sent to Wörwag Pharma GmbH & Co. KG, where it is stored safe and strictly closed. A duplicate of the randomization list will also be stored in a safe by the statistician [name]. [name] for safety reasons, if the original list gets lost. After correct data unblinding by the original list, this duplicate list will be eliminated.

Additionally to the randomizing list for packaging of the study medication, two sets of sealed envelopes are prepared by the statistician for emergency purposes. Each envelope contains the allocation to the study medication for an individual patient. One set of sealed envelopes will be sent to the investigator, one set will be safely stored at Wörwag Pharma GmbH & Co. KG. If a serious adverse event occurs that requires the unblinding of a single patient, this will be performed by opening the envelope of this patient.

The reason for and the date of unblinding has to be documented on the envelope and in the CRF. All other patients remain blinded.

After the end of the study, all envelopes of the investigator have to be sent to the biometric centre. The integrity of the envelopes has to be documented by a third party.

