## Withdrawal of individual subjects

Subjects can leave the study at any time for any reason if they wish to do so without any consequences. The investigator can decide to withdraw a subject from the study for urgent medical reasons.

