### Specific criteria for withdrawal

- Serious adverse events
- Hospitalization of the patient
- Non compliance of the patient
- Change of concomitant medication which might influence the primary and secondary endpoints itself (e.g. ACE-inhibitors, AT II-antagonists)

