# SAFETY REPORTING

## Section 10 WMO event

In accordance to section 10, subsection 1, of the WMO, the investigator will inform the subjects and the reviewing accredited METC if anything occurs, on the basis of which it appears that the disadvantages of participation may be significantly greater than was foreseen in the research proposal. The study will be suspended pending further review by the accredited METC, except insofar as suspension would jeopardize the subjects’ health. The investigator will take care that all subjects are kept informed.

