## Adverse and serious adverse events

Adverse events are defined as any undesirable experience occurring to a subject during a clinical trial, whether or not considered related to the investigational drug. All adverse events reported spontaneously by the subject or observed by the investiga­tor or his staff will be recorded.
A serious adverse event is any untoward medical occurrence or effect that at any dose results in death;

- is life threatening (at the time of the event);
- requires hospitalization or prolongation of existing inpatients’ hospitalization;
- results in persistent or significant disability or incapacity;
- is a congenital anomaly or birth defect;
- is a new event of the trial likely to affect the safety of the subjects, such as an unexpected outcome of an adverse reaction, lack of efficacy of an IMP used for the treatment of a life threatening disease, major safety finding from a newly completed animal study, etc.

All SAEs will be reported to the accredited METC that approved the protocol, according to the requirements of that METC.

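### Section 8.2.1 requires contact with the medical monitor before every unblinding, with no exception for an emergency or an unreachable monitor

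*Protocol*

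**What the plan says.** Protocol section 7.2 (Randomisation, blinding and treatment allocation) describes how a single patient's code is broken. It provides that "two sets of sealed envelopes are prepared by the statistician for emergency purposes". On where they are kept it says: "One set of sealed envelopes will be sent to the investigator". The other set is stored at the company supplying the study drug. If a serious adverse event makes it necessary to unblind a patient, "this will be performed by opening the envelope of this patient", and the reason and date are noted on the envelope and in the case report form. Section 7.2 mentions no medical monitor and does not refer to section 8.2.1.

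Section 8.2.1 (SUSAR), after the expedited-reporting deadlines, states: "For all events that may require the unblinding of participant treatment, the medical monitor must be contacted before the unblinding occurs". The monitor then informs the protocol chairs and the medical officer. A written account must give the reason, the name of the monitor who was informed, and the date and time of unblinding. A participant who is unblinded stops study treatment and leaves the trial.

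**The concern.** Envelopes are held on site so that the treating side can learn the allocation without delay. The definition of a serious adverse event in section 8.2 includes the entry "is life threatening (at the time of the event", so the envelope procedure covers cases in which there may be little time. A contact-first rule without exception works against the envelopes in those cases.

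Two things are at stake. A patient's care could be held up while the monitor is sought, or a physician who acts at once in the patient's interest could be recorded as having deviated from the protocol. There is also a practical gap: an investigator who follows section 7.2 alone would break the rule in section 8.2.1 without knowing that it exists.

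**Working it through.** The point concerns procedure text. The protocol gives no figure to reproduce, so the check compares the sections.

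1. **Scope of the rule.** Section 8.2.1 covers every event that may call for unblinding, makes contact mandatory and puts it first. The code break for a serious adverse event in section 7.2 therefore falls within it.

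2. **Can both sections be followed?** Section 7.2 says how the code is broken; section 8.2.1 says whom to contact first. Section 7.2 is silent on a prior step and does not exclude one. Section 8.2.1 asks for contact, not for permission or a waiting period. With a reachable monitor, the investigator makes contact, opens the envelope and has followed both.

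3. **Where the sequence fails.** Suppose care is urgent, depends on the allocation, and the monitor cannot be reached. Only two courses remain: wait, or open the envelope and deviate. Sections 7.4 to 7.7 and 8.1 to 8.3 contain no exception or fallback for unblinding.

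4. **How urgency is handled elsewhere.** Section 7.4: "The investigator can decide to withdraw a subject from the study for urgent medical reasons". Section 8.1: "The study will be suspended pending further review by the accredited METC, except insofar as suspension would jeopardize", where the ground named is the health of the subjects. Neither provision governs unblinding, so neither fills the gap. They show only that the protocol allows for urgency in other decisions.

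5. **What prior contact protects in an emergency.** An unblinded participant is taken out of the trial in any case (section 8.2.1), and the first withdrawal criterion in section 7.4.1 is "Serious adverse events". For a patient with such an event, prior contact therefore preserves little.

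6. **How often this could matter.** The Summary names only rare urticaria and pruritus as known risks. Section 6.5 describes very low toxicity, reports no serious adverse events in clinical studies of benfotiamine so far, and allows for single allergic reactions. The protocol gives no rate of emergency code breaks and no figure for a delay, so neither can be computed.

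**The case against.** The strongest reply is that nothing here is inconsistent and that harm is hypothetical. The two sections can be followed in order, and a call or message before opening the envelope may be enough to comply. The study drug is a thiamine derivative added to existing treatment (section 3). A physician can usually stop the tablets and treat the patient as if on active drug, without the code. The investigator can also withdraw a patient for urgent reasons without contacting anyone first. Finally, the sentence stands in the SUSAR subsection and may have been written with reporting in mind, while emergency code breaks have their own text in section 7.2.

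Much of this stands. It rules out a stronger reading that a reader might infer: that sections 7.2 and 8.2.1 contradict each other, or that the investigator needs the monitor's consent. The text supports neither. Nor can one infer that the monitor would be hard to reach; contact pages are absent from the public copy, and that absence is no fault of the plan. The low risk of the product makes it unlikely that a code break would change urgent care.

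Two parts of the reply do not remove the point. The wording of section 8.2.1 covers all events and is not limited to SUSAR reporting. And rarity limits the importance of the gap, but does not justify a rule that works badly in the situation for which the envelopes were prepared.

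**Conclusion.** The point holds as a minor matter of patient safety, to be considered at the next revision. As written, the rule leaves the physician to wait or deviate when three things coincide: care is urgent, it depends on the allocation, and the monitor cannot be reached. On the protocol's own account of the product, that should be rare. The size of the risk cannot be given from the protocol, and none is assumed.

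A reader might also infer some damage to the trial's statistical conclusions. There is none: the rule on contact does not alter the significance level, the power or the primary analysis. The verdict rests on a literal reading of section 8.2.1. If the sponsor meant the rule only for unblinding in connection with SUSAR reporting, the text should say so, and the same edit would serve.

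**What to change.** In section 8.2.1, state that when urgent care depends on the allocation, the investigator may open that patient's envelope under section 7.2 at once and notifies the medical monitor as soon as possible afterwards. Keep prior contact for all other unblinding, including unblinding for SUSAR reporting. Add cross-references between sections 7.2 and 8.2.1. Keep the written account and record in it both the time of opening and the time of notification; it already asks for the date and time of unblinding, so only the second entry is new.

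The cost is a few sentences of protocol text. No staff, visits or materials are added, since the investigator already holds the envelopes. The downside is that the monitor cannot advise before an emergency code break, so an occasional avoidable unblinding may occur. That patient would leave the trial and be replaced under section 7.5, which admits further patients until the planned number is reached.

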### Annual safety report

In addition to the expedited reporting of SUSARs, the sponsor will submit, once a year throughout the clinical trial, a safety report to the accredited METC, competent authority, Medicine Evaluation Board and competent authorities of the concerned Member States.

This safety report consists of:

- a list of all suspected (unexpected or expected) serious adverse reactions, along with an aggregated summary table of all reported serious adverse reactions, ordered by organ system, per study;

- a report concerning the safety of the subjects, consisting of a complete safety analysis and an evaluation of the balance between the efficacy and the harmfulness of the medicine under investigation.

## Follow-up of adverse events

All adverse events will be followed until they have abated, or until a stable situation has been reached. Depending on the event, follow up may require additional tests or medical procedures as indicated, and/or referral to the general physician or a medical specialist.

# STATISTICAL ANALYSIS

## Descriptive statistics

First, study patients will be described with their demographical and medical data. This will be done for the entire study population to describe study patients. Additionally this will be done separately for each of the two groups to investigate comparability of the groups (which might be disturbed due to drop-outs). Further, all outcome variables will be evaluated with descriptive statistical methods. For quantitative variables this includes maximum, median, mean, minimum as well as standard deviation. For qualitative variables absolute and relative frequencies will be used.

## Confirmatory testing

Primary outcome variables are the differences of β2-microglobulin and albumin in 24 hour urine between end and start of study medication. Both primary outcome variables will be tested with the t-test for independent samples. In case the distribution of the variables is clearly not a normal distribution, then the t-test will be replaced by the Wilcoxon test. To solve the problem of multiple confirmatory testing the p-values of the two tests will be adjusted by the Bonferroni-Holm procedure. The level of significance is established as 2.5% for the one-sided hypotheses excretion with verum is less at the end of the medication phase than excretion with placebo.

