## Sample size calculation

The two primary outcome variables are quantitative. As primary outcome measure, the difference between the value at the end and the value at the start of medication is defined. It is assumed that the differences are normally distributed. P-values are adjusted for multiple testing by the Bonferroni-Holm-procedure. Hypotheses are one sided. As level of significance 2.5% are established.

It is proposed to have 38 evaluable patients per group. This sample size enables the study to detect an effect of size 0.65 with a power of 80%. Effect size is the difference in group means divided by the common standard deviation. For clarification: If (mean of the placebo group minus the mean of the verum group ) divided by the standard deviation is bigger or equal 0.65 then the study will deliver a significant result with a probability of at least 80%.

The drop-out rate is assumed to be 10%. Therefore 43 patients have to be randomised to each group to have 38 evaluable patients. For both groups together 86 patients are needed for admission to the study.

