## Study procedures

The patients will be instructed in advance how to collect the 24-hour urine in the previous day, and will be asked to refrain from food from the previous evening to take fasting blood samples

The subjects will visit the clinic 5 times during this clinical trial. Two times in the run in phase, one time directly before the beginning of the treatment phase, one time in the middle of the treatment phase, and one last time at the end of the treatment phase. They will be instructed in advance how to collect the 24-hour urine in the previous day, and will be asked to refrain from food from the previous evening to take fasting blood samples

In each visit the following procedures will be applied:

- Samples of 24-hour urine will be received from the patients and sent to the laboratory for analysis. The primary and secondary study parameters will be measured in the 24-hour urine of the preceding day.

- Second-morning urine samples will be collected and sent for analysis.

- Fasting blood samples will be drawn and sent for analysis.

- Weight and blood pressure will be measured.

- Compliance with the intake of the benfotiamine or placebo will be ensured by counting the pills in the last two visits of each patient.

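### The primary test on change ignores the baseline value already collected; adjusting for it would recover part or all of the power lost at the first Holm step, depending on the start-end correlation

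*Protocol*

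**What the plan says.** Protocol section 4.4 (Sample size calculation) sets the primary outcome for each of the two markers: "the difference between the value at the end and the value at the start of medication is defined". Section 9.2 (Confirmatory testing) then fixes the test: "Both primary outcome variables will be tested with the t-test for independent samples", with a Wilcoxon test instead if the distribution is clearly not normal. Neither section names a baseline covariate.

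On error control, section 4.4 states "Hypotheses are one sided", "As level of significance 2.5% are established" and "P-values are adjusted for multiple testing by the Bonferroni-Holm-procedure".

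Section 7.3 (Study procedures) lists five visits: "Two times in the run in phase, one time directly before the beginning of the treatment phase", then one mid-treatment and one at the end. For every visit it says: "The primary and secondary study parameters will be measured in the 24-hour urine of the preceding day". A week-0 value of both primary markers is therefore planned for each patient, as are two run-in values.

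**The concern.** A t-test on change subtracts one 24-hour collection from another. That gives the baseline a fixed weight of one, however well or badly it predicts the end value. Unless the start-end correlation is perfect, this weight is too large, and noise in the start value is carried into the outcome. ANCOVA estimates the weight from the data.

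The choice matters here because the trial is small and has little power to spare. The sample size in section 4.4 was worked out at the full one-sided 2.5%, although the same section calls for a Holm adjustment over two outcomes. Precision available from data already collected is therefore worth having. The protocol does not leave the model open for a later document; it names the unadjusted test as the confirmatory one.

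**Working it through.** **Inputs from section 4.4:** effect size d = 0.65 on the change score (SD standardised to 1), 38 evaluable per group, one-sided 0.025, Holm over two outcomes, 10% drop-out. **Assumed:** the start-end correlation ρ, which the protocol does not state (shown from 0.3 to 0.95), normality, and equal variances at start and end.

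**1. The plan's own figure.** n = 2(1.960 + 0.842)²/0.65² ≈ 37.2, so 38 per group; 38/0.9 = 42.2, so 43 per group and 86 in all. Power with 38 per group at 0.025 is 80.9% by the normal approximation and 79.9% by the noncentral t. The stated numbers reproduce, but only at the full 0.025.

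**2. First Holm step.** The smaller p-value is compared with 0.025/2 = 0.0125. The noncentrality is 0.65·√(38/2) = 2.833 on 74 df, and power is 70.7% (normal approximation 72.3%). The loss is 79.9 − 70.7 = 9.2 points.

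**3. Variance of the two analyses.** With common variance σ² at each time:
- change score: 2(1−ρ)σ²
- ANCOVA residual: (1−ρ²)σ²
- ratio: (1−ρ)(1+ρ)/[2(1−ρ)] = (1+ρ)/2

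The equivalent effect size is 0.65/√((1+ρ)/2), tested on 73 df.

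**4. Power at one-sided 0.0125, 38 per group, week-0 value as covariate.**

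| ρ (assumed) | variance ratio | equivalent d | power | share of 9.2 points recovered |
|---|---|---|---|---|
| unadjusted | 1 | 0.650 | 70.7% | – |
| 0.3 | 0.650 | 0.806 | 88.7% | all |
| 0.5 | 0.750 | 0.751 | 83.5% | all |
| 0.7 | 0.850 | 0.705 | 78.2% | 82% |
| 0.8 | 0.900 | 0.685 | 75.6% | 54% |
| 0.9 | 0.950 | 0.667 | 73.1% | 26% |
| 0.95 | 0.975 | 0.658 | 71.9% | 13% |

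Recovery is complete for ρ up to about 0.64 and more than half for ρ up to about 0.81.

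These figures charge ANCOVA 1 df only. Estimating the slope also inflates the variance on average by 1/(2·38 − 4) = 1/72, about 1.4%. That takes some 0.6 points off each power between ρ = 0.5 and 0.9 and does not change the pattern.

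**5. What the 70.7% means.** It is the power for an outcome when the other has no effect. Simulating Holm with effects of 0.65 on both outcomes, and a correlation between them from 0 to 0.8, gives 75–77% for a given outcome, 79–91% for at least one and 63–71% for both.

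**6. Chance imbalance.** If the groups differ by δ at baseline, the change-score difference shifts by −(1−ρ)δ given that imbalance: half of δ at ρ = 0.5, a fifth at ρ = 0.8. Averaged over randomisations the shift is zero.

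**7. All three pre-treatment values.** If all visits are equally correlated, taking their mean as covariate gives a variance ratio of [1 − 3ρ²/(1+2ρ)]/[2(1−ρ)] against the week-0 change score, and power of at least 88% for ρ up to 0.95. If correlation decays in a first-order pattern, the run-in values add nothing and the table in step 4 applies.

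**The case against.** The planned test is not an error. In a randomised double-blind trial the t-test on change is unbiased and keeps its type I error, and it matches the outcome on which the trial was sized. This stands: the point is one of efficiency.

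The gain depends on a correlation that the protocol does not give. This also stands. A reader might infer that adjustment would restore most of the lost power whatever the data look like. The documents do not support that, and for ρ above about 0.81 the week-0 covariate recovers less than half.

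A reader might also infer that true power is 71% for each endpoint. Section 4.4 does not say which power its 80% refers to, and 70.7% is the case of an effect on one outcome only. The Holm shortfall itself belongs to the sample size calculation and is not a fault of the t-test.

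A reader might see a contradiction in section 9.2, which defines the outcome as a change but words the hypothesis as "excretion with verum is less at the end of the medication phase than excretion with placebo". There is none on the mean scale: randomisation makes expected baselines equal, so lower excretion at the end and a larger fall are the same hypothesis.

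Finally, if the Wilcoxon test is used instead, these power figures do not apply directly. That test is also unadjusted, so the baseline information is still left out.

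**Conclusion.** The point holds as a conditional gain in precision. Section 9.2 fixes an unadjusted comparison of change although the week-0 value is collected. Under equal variances, ANCOVA on that value has (1+ρ)/2 of the variance, at the cost of one estimated slope. At the first Holm step the gain over 70.7% is about 13 points at ρ = 0.5, 7 to 8 at 0.7, 5 at 0.8 and 2 to 3 at 0.9. The unknown ρ governs the size of the benefit, but it does not reverse the recommendation anywhere in the range shown. Baseline imbalance is a source of variance here, scaled by 1−ρ, and not a systematic bias. The figures rest on normality, equal variances and the protocol's own effect of 0.65 on the analysed scale.

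**What to change.** In section 9.2, before unblinding, replace the independent-samples t-test with ANCOVA of week-12 excretion on treatment and the week-0 value, for each primary marker. Keep one-sided 2.5% with Holm. Report the unadjusted test on change as a sensitivity analysis.

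If excretion is log-transformed because of skewness, say so in the same amendment. The estimand then becomes a ratio of geometric means, and the effect size of 0.65 and the powers above must be read on the log scale; they do not carry over from the raw change.

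Averaging the two run-in values into the baseline is optional. Its gain depends on the between-visit correlation. It may be reduced because patients are selected on 30–300 mg/24 h before inclusion (section 4.2) and because treatment is optimised during run-in (section 5.2).

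The cost is a protocol amendment and one model parameter. With the week-0 covariate, no further patients, visits or samples are needed.

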## Inclusion criteria

• Type 2 diabetes mellitus
• Age: 40-75 years
• Patients are on treatment with angiotensin converting enzyme inhibitors (ACEi) and/or angiotensin II antagonists (AIIA) in an unchanged dose for at least 3 months
• Active diabetic nephropathy as indicated by presence of microalbuminuria (30-300 mg/24 h urine) in at least two samples within 2-6 weeks in advance of inclusion in the trial
• HbA1c < 8.5%, a higher HbA1c  9.5% is acceptable if the treating physician and the patient have accepted that striving for lower values is an unreachable goal (patients with high HbA1c values are the ones that one would expect to be benefit most from treatment with benfotiamine)
• eGFR (estimated by MDRD formula) > 30 ml/min
• Males and postmenopausal females
• Written informed consent

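### Both primary markers are compared as unadjusted raw changes with a data-driven switch to Wilcoxon; a prespecified log-scale analysis adjusted for baseline would probably be more efficient, at little cost

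*Protocol*

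**What the plan says.** Protocol section 9.2 defines the endpoint on the raw scale: "Primary outcome variables are the differences of β2-microglobulin and albumin in 24 hour urine between end and start of study medication". It fixes the test: "Both primary outcome variables will be tested with the t-test for independent samples". It then adds a fallback: "In case the distribution of the variables is clearly not a normal distribution, then the t-test will be replaced by the Wilcoxon test". The protocol does not say how or by whom the distribution is judged, or whether this happens before unblinding.

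Section 4.4 sizes the trial on the same footing: "It is assumed that the differences are normally distributed". It gives 38 evaluable patients per group for a standardised difference of 0.65 with 80% power. The error rate is set by "Hypotheses are one sided" and "As level of significance 2.5% are established", with Bonferroni-Holm over the two variables.

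Section 4.2 sets the albumin range at entry: "Active diabetic nephropathy as indicated by presence of microalbuminuria (30-300 mg/24 h urine", in at least two samples. There is no entry range for β2-microglobulin. No log transformation, ratio or baseline covariate appears anywhere in the protocol.

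**The concern.** The entry range for albumin is tenfold. If a patient's excretion varies, or responds to treatment, roughly in proportion to its level, a 30% fall is 9 mg/24 h from a start of 30 and 90 mg/24 h from a start of 300. Pooling such changes in mg gives a long-tailed distribution in which the few patients near the upper limit carry most of the variance. The t-test then loses efficiency. The fallback to Wilcoxon recovers some of it, but it still ranks changes in mg.

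The switch also means that the confirmatory test, and whether it addresses a difference in means or a shift in ranks, is settled only after the trial data are inspected. What is at stake is power in a small trial and a clear prespecified estimate, more than the false-positive rate.

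**Working it through.** **1. The plan's own figure.** For a difference of 0.65 SD, one-sided α = 0.025 and 80% power:

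n per group = 2 × (1.960 + 0.842)² / 0.65² = 2 × 7.85 / 0.4225 ≈ 37.2, rounded up to 38.

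Exact t-test power at 38 is 0.7985. With 10% drop-out, 38 / 0.9 = 42.2, rounded up to 43 per group and 86 in total. The protocol's numbers reproduce for one test at the full 2.5% on normally distributed differences.

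**2. What the entry range implies.** If log change has SD σ, the SD of the raw change from a fixed start b is b × exp(σ²/2) × √(exp(σ²) − 1). With σ = 0.5 (an assumption) the multiplier is 1.133 × 0.533 = 0.604. That gives about 18 mg/24 h at b = 30 and 181 mg/24 h at b = 300. Each arm is therefore a mixture of very different spreads.

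**3. Simulation.** The protocol gives no SD or distribution for either marker, so these inputs are assumptions:
- true log albumin normal, centred at 90 mg/24 h with SD 0.7, and two run-in values both within 30-300;
- within-patient log SD 0.3, 0.4 or 0.5, so the SD of log change is √2 times that: 0.42, 0.57 or 0.71;
- proportional effect of 0.65 SD of log change, i.e. a ratio of exp(−0.65 × 0.42) = 0.76 down to exp(−0.65 × 0.71) = 0.63;
- 38 per group, one endpoint, one-sided 2.5%;
- the undefined switch modelled as Shapiro-Wilk p < 0.01 on residuals.

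| Analysis | Power over the three settings |
|---|---|
| t-test on raw change | 0.54-0.61 |
| Planned rule (t-test, switch to Wilcoxon) | 0.64-0.69 |
| ANCOVA on the raw scale | 0.75-0.79 |
| t-test on log change | 0.78-0.81 |
| ANCOVA on the log scale | 0.86-0.90 |

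Type I error stays near 2.5% with a fixed gate. The gate fired in about 68-83% of trials with an effect. In a second model with a 5% gate, which also covered wider baselines, it fired in 84-100%.

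**4. The same effect on the protocol's scale.** In this model, 0.65 SD of log change equals only about 0.46-0.52 SD of raw change. When the proportional effect is enlarged to about 0.58-0.67 raw SD, the planned rule reaches 0.84-0.89.

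**5. The opposite model.** Let change be additive with the same SD in mg (20 or 40) at every start between 30 and 300, and the effect 0.65 of that SD. The raw t-test then has power 0.78-0.80 and the log-change t-test 0.49-0.50. Log ANCOVA was not run in this model.

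**The case against.** Four stronger readings are tempting, and the protocol does not support them.

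*The stated 80% power is missed.* Section 4.4 defines 0.65 as a raw mean difference over the common raw SD. The simulation sets 0.65 on the log scale, so the log-change t-test has about 80% by construction and the raw analyses face a smaller raw effect. On the protocol's own definition the planned rule does at least what is claimed (step 4).

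*The common-SD assumption is broken.* The common SD in section 4.4 is common to the two groups, not to patients with different starting levels. Randomisation gives both arms the same mix. In the model the raw-change SDs (verum against placebo) were 50 and 53, 67 and 75, and 88 and 101 mg/24 h. The 18 against 181 in step 2 explains the long tails and is not a breach of that assumption.

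*The switch inflates the type I error.* A fixed gate does not. Taking the better of two p-values would give about 3-4%, but section 9.2 ties the switch to the distribution and not to the result. The criterion and its timing could also be settled in a statistical analysis plan that is not at hand.

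*A switch leaves no effect size.* Section 9.1 requires mean and SD for all quantitative outcomes, whichever test is used.

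Two limits also stand. The advantage rests on proportional variation, and step 5 shows the log-change t-test losing clearly if that is wrong. Part of the gain comes from the baseline covariate: raw-scale ANCOVA alone reaches 0.75-0.79.

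What the objection does not remove is that the protocol itself fixes an unadjusted raw-scale comparison. The model that favours it needs a patient at 30 mg/24 h to vary by as many mg as one at 300, which is hard to credit.

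**Conclusion.** The point holds as an improvement in efficiency and clarity; the plan is not in error on its own terms. For albumin, with log-normal excretion and proportional effects, a prespecified log-scale analysis with the week-0 value as covariate raises power from about 0.64-0.69 under the planned rule to about 0.86-0.90 at the same sample size. The log scale and the covariate each contribute. It also removes a choice of test that would otherwise often be made after seeing the data.

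The size of the gain depends on assumed variability. It was computed for one endpoint at the full 2.5%, and it has not been shown for β2-microglobulin, for which the protocol gives neither a range nor any data.

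**What to change.** In section 9.2, prespecify for both primary variables a comparison of log week-12 excretion between groups, adjusted for log week-0 excretion, reported as a ratio of geometric means with confidence interval. Remove the data-driven switch and keep Wilcoxon as a sensitivity analysis. In section 4.4, state that 0.65 then refers to the SD on the log scale. The adjusted comparison also matches the one-sided hypothesis in section 9.2, which is worded in terms of excretion at the end of the medication phase.

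No extra patients, visits or samples are needed, since both 24-hour collections are already planned. The costs are these:
- the effect is expressed as a percentage and not in mg/24 h;
- 0.65 is redefined and needs its own justification on the new scale;
- undetectable β2-microglobulin values need a substitution rule fixed in advance, with a sensitivity check, because the substituted value can matter on the log scale.
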